## 5.6 Endpoint

The primary outcome measure was live birth rate and the secondary outcome measures were included clinical pregnancy rate, miscarriage rate, implantation rate and so on.

# 6 Subjects selection

Inclusion criteria:

1. Date from September 1^st^, 2010 to January 31^st^, 2013
2. Hormone replacement FET cycles;
3. Subjects with age ≥20 and ≤40 years old;
4. With d3 frozen embryos;
5. Endometrial thickness ≥7mm on the day of secretory transformation;
6. Agreed to sign informed consent form。

Exclusion criteria were in hormone replacement FET cycles

1. Patients with uterine disorders, such as uterine malformations (unicornuate uterus, bicornuate uterus, mediastinal uterus, double uterus), adenomyosis, submucosal fibroids and intrauterine adhesion;
2. Suffered 3 or more spontaneous abortions (including biochemical pregnancy);
3. Embryo transfer in patients failed for 3 or more times (including biochemical pregnancy);
4. Patients not suitable for assisted reproductive technology;
5. Patients that were taking medication or treatment having influence on reproductive and metabolic function, including diabetes drugs, anti-hypertensive drugs (diazoxide, ACEI inhibitors, calcium channel blockers), Chinese herbal medicine and acupuncture;
6. Endometrial thickness <7mm on the day of secretory transformation;
7. Patients who can’t comply with the study protocol.

# 7 Physical examination

Physical examination was conducted and patient's vital signs (temperature, heart rate, respiration and blood pressure), height, weight, and gynecological examination were recorded. Patients with elevated blood pressure (≥160/100) were measured again 15 minutes after the sit-in.

# 8 Transvaginal ultrasound examination

Uterine size, whether there is fibroid and its size, uterine abnormalities (uterine malformations, adenomyosis, endometrial echogenic mass), endometrial thickness, size and shape of the ovaries were inspected. Ovary size was determined by measuring the maximum plane in two dimensions.

# 9 Outcome measures

The primary outcome measure was live birth rate and the secondary outcome measures were included clinical pregnancy, miscarriage, ectopic pregnancy and implantation rates.

# 10 Duration

From September 1^st^, 2010 to January 31^st^, 2013, patients who received hormone replacement FET cycles at Reproductive Medicine Center of Renji Hospital and satisfied inclusion criteria were enrolled in the study. 10 months after transfer, patients were followed-up to investigate birth outcomes. From enrollment to follow-up completed, it would take 28 months (from September 1^st^, 2010 to December 31^st^, 2013).

# 11Data statistics

## 11.1 Estimation of sample size

Yanushpolsky, et al reported in a RCT study that ongoing pregnancy or live birth rates in sustained release vaginal progesterone gel and intramuscular progesterone groups were 45.2% and 42.2%, respectively, in FET cycles ^[3]^. Two domestic studies were reported respectively that clinical pregnancy rate in 155 patients who received intramuscular progesterone in hormone replacement FET cycles to promote endometrium to secretory phase was 34.8% and in 315 patients was 23.5% ^[8-9]^. Assuming that live birth rate in sustained release vaginal progesterone gel group in hormone replacement FET cycles was 10% higher than that in intramuscular progesterone group (40% in sustained release vaginal progesterone gel group and 30% in intramuscular progesterone group), 675 cycles were required to reach 90% statistical power for each group. Considering about 10% of dropout rate, 750 cycles were required for each group and a total of 1500 cycles for 2 groups.

Calculation of sample size

Significance level α: 0.01

1-β: 0.90

Live birth rate in group A: 0.40

Live birth rates in group B: 0.30

Ratio: 1:1

The minimum sample size: 675 cycles for each groups and a total of 1350 cycles for 2 groups.

Considering about 10% of dropout rate, 750 cycles were required for each group and a total of 1500 cycles for 2 groups.

## 11.2 Statistical methods

Differences in live birth rates between the two groups were discussed using intentional analysis. Data were compared using statistical software SPSS 19.0. Results were expressed as mean ± standard deviation (X ± SD) or percentage (%).Count data was analyzed using chi-square test and measurement data using T-test.

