# 5 Design

## 5.1 Overall design

This study was a single-center, prospective, randomized (1: 1) clinical trial. The comparison of live birth rates between sustained release vaginal progesterone gel and intramuscular progesterone in hormone replacement FET cycles was carried out. 1500 patients were recruited and randomly divided into two groups. Patients in group A were received sustained release vaginal progesterone gel and in group B received intramuscular progesterone.

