## 5.4 Endometrial secretory transformation and luteal phase support

Group A: On the day of endometrial secretory transformation (D0), patients were administrated sustained release vaginal progesterone gel 90mg/d, dydrogesterone 20mg/d orally and estradiol valerate 4-8 mg/d. Embryo with top score on D3 FET was administrated at the same dose continually to the 14 days after transfer. The number of transferred embryos was defined in accordance with standards of Ministry of Health. For subjects <35 years old with first embryo transfer, 2 embryos were allowed to transfer at most; for subjects ≥ 35 years old or with re-transfer, 2-3 embryos were allowed.

Group B: On the day of endometrial secretory transformation (D0), patients were administrated intramuscular progesterone 40 mg/d, dydrogesterone 20mg/d orally and estradiol valerate 4-8 mg/d. Embryo with top score on D3 FET was administrated at the same dose continually to the 14 days after transfer. The number of transferred embryos was defined in accordance with standards of Ministry of Health. For subjects <35 years old with first embryo transfer, 2 embryos were allowed to transfer at most; for subjects ≥ 35 years old or with re-transfer, 2-3 embryos were allowed.

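### Implantation rate is undefined, and the chi-square rule in 11.2 would most naturally be applied to embryos, ignoring that embryos transferred to one woman are clustered

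*Combined protocol and SAP*

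**What the plan says.** Section 11.2 names two tests for the whole trial: "Count data was analyzed using chi-square test and measurement data using T-test". It adds that "Results were expressed as mean ± standard deviation (X ± SD) or percentage", so an outcome reported as a rate falls most naturally under the chi-square rule. No method for correlated observations appears anywhere.

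Section 9 states that "secondary outcome measures were included clinical pregnancy, miscarriage, ectopic pregnancy and implantation rates". Sections 3 and 5.6 also list implantation rate. None of the three gives a numerator, a denominator or a unit of analysis.

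Section 5.4 sets the number of embryos. "For subjects <35 years old with first embryo transfer, 2 embryos were allowed to transfer at most", so one embryo is possible in that group; "for subjects ≥ 35 years old or with re-transfer, 2-3 embryos were allowed".

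Sections 5.1 and 5.2 randomise patients. The CRF records one count of embryos transferred per woman (embryo transfer form) and one count of intrauterine gestational sacs per woman (clinical pregnancy form).

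**The concern.** If implantation rate is sacs divided by embryos transferred, the chi-square table has embryos in its cells. Randomisation was of women, and embryos placed in the same woman share her uterus, the source of the embryos and the assigned progesterone. Their outcomes are likely to be positively correlated. The chi-square test assumes that they are independent.

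With positive correlation the usual standard error is too small, the confidence interval too narrow and the p-value too low. A chance difference in implantation between the two progesterone routes could then be reported as significant more often than the nominal level allows.

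**Working it through.** **The plan's own figure.** Section 11.1 uses live birth rates of 0.40 and 0.30, α = 0.01, power 0.90 and a 1:1 ratio. The two-sided formula with pooled variance and no continuity correction is

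n = [z(0.995)·√(2·0.35·0.65) + z(0.90)·√(0.40·0.60 + 0.30·0.70)]² / 0.10²

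= [2.576 × 0.6745 + 1.282 × 0.6708]² / 0.01 = 674.5, so 675 per group.

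Then 675 / 0.90 = 750. Both figures reproduce. They concern live birth, counted once per cycle, so embryo clustering does not touch them.

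**Inputs for implantation.** From the documents: up to two, or two to three, embryos per woman (5.4) and about 750 women per arm (11.1). Assumed, because the documents do not give them: the intra-woman correlation (ICC) and the mix of embryo numbers. Both are shown as a range.

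**Formulas.** With m embryos per woman, the design effect is DE = 1 + (Σm²/Σm − 1) × ICC. The true standard error is √DE times the one used by the embryo-level test. The true two-sided error is 2 × [1 − Φ(z(1−α/2)/√DE)].

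**Worked example.** With 75% of women receiving two embryos and 25% three, Σm²/Σm = (0.75×4 + 0.25×9)/(0.75×2 + 0.25×3) = 5.25/2.25 = 2.33, so DE = 1 + 1.33 × ICC. At ICC 0.4, DE = 1.53, and 1.96/√1.53 = 1.58 gives a true error of 11.3%.

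| Assumed mix | DE at ICC 0.1 to 0.4 | True error, nominal 5% | True error, nominal 1% |
|---|---|---|---|
| 20% one, 80% two | 1.09 to 1.36 | 6.0% to 9.2% | 1.4% to 2.7% |
| all two | 1.10 to 1.40 | 6.2% to 9.8% | 1.4% to 3.0% |
| 20% one, 60% two, 20% three | 1.12 to 1.48 | 6.4% to 10.7% | 1.5% to 3.4% |
| 75% two, 25% three | 1.13 to 1.53 | 6.6% to 11.3% | 1.6% to 3.8% |

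The 1% column is included because 11.1 uses α = 0.01, while 11.2 states no level for secondary outcomes. At ICC 0 there is no inflation. As an extreme, all women receiving three embryos at ICC 0.5 gives DE = 2.00 and a true error of 16.6% at nominal 5%.

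**Simulation check.** 8,000 null trials were simulated with beta-binomial outcomes, 750 women per arm, 80% receiving two embryos and 20% three, and 30% implantation (assumed). At ICC 0.1, 0.3 and 0.5 the embryo-level chi-square rejected 6.1%, 9.5% and 12.6% at nominal 5%. A ratio estimator with variance clustered on the woman rejected 4.5%, 5.0% and 5.0%.

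**Effect on precision.** Assume 30% implantation and two embryos in each of 750 women per arm (1,500 embryos). The 95% half-width for the difference is 1.96 × √(2 × 0.21/1500 × DE). It is 3.3 percentage points with no correlation, 3.4 at ICC 0.1 and 3.9 at ICC 0.4.

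**The case against.** The strongest reply is that the embryo-level test is inferred. Implantation rate is undefined, and 11.2 also allows a t-test for measurement data. A per-woman implantation proportion compared by t-test would fit 11.2 as written and would avoid the problem. This stands as a limit on certainty, but the plan does not choose that analysis. The outcome is called a rate, it is listed apart from clinical pregnancy, and the CRF collects exactly the two counts needed for sacs per embryo. The embryo-level chi-square remains the natural reading.

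It is also fair that the size rests on assumptions. The documents report no ICC and no embryo mix. Section 5.4 permits single transfers, which add no clustering. The table allows for them, and they lower the inflation without removing it.

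A reader might go further. Section 11.1 says "750 cycles were required for each group and a total of 1500 cycles for 2 groups", while 5.1 says "1500 patients were recruited and randomly divided into two groups". From this one might infer that women re-entered after a failed cycle, so that the primary comparison also suffers from non-independence. The documents do not support that. Sections 5.1 and 5.2 randomise 1500 patients with 1500 random numbers, and nothing shows that any woman was randomised twice. Nor would freshly randomised repeat cycles inflate error in the same way, since each would have its own allocation, whereas embryos in one woman all share one arm. In 8,000 simulated null trials with about 390 re-entries among about 1,540 cycles (ICC 0.4), the naive test rejected 4.7% at nominal 5% and 0.9% at nominal 1%. The patients/cycles difference is at most a wording inconsistency.

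**Conclusion.** The point holds for one secondary outcome. Read in the natural way, 11.2 would compare implantation rate by a chi-square test on embryos, which ignores clustering within women and overstates precision if the within-woman correlation is positive. For ICC 0.1 to 0.4 and mostly two-embryo transfers, with some single or triple transfers, the true standard error is about 1.04 to 1.24 times the naive one. A nominal 5% test then has a true error of about 6% to 11%.

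This rests on three things the documents do not state: the embryo denominator, a positive correlation and the mix of embryo numbers. A reader might infer that the live birth result or the sample size is undermined; neither is. The change should be made, but the trial's main conclusion does not depend on it.

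**What to change.** In 11.2, define implantation rate as intrauterine gestational sacs divided by embryos transferred, among women who had a transfer. The restriction is needed because the CRF foresees randomised women with no transfer, for whom the ratio does not exist; report their number by arm.

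For this outcome, replace the chi-square test with one of the following, named in advance:

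- an analysis of sacs over embryos clustered on the woman, by logistic GEE or a ratio estimator with robust variance; or
- a t-test of per-woman implantation proportions, which weights women equally and uses a test that 11.2 already names.

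The cost is a few sentences in 11.2 and a somewhat wider interval. The counts are already on the CRF, and no extra patients or visits are needed. Section 6 needs no change for this point.

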**Into-group conditions（****Answer requiring to be "YES"）**

1. The patient's age at the time of informed consent≥20y and ≤40y？□Yes □ No
2. Is the patient have d3 frozen embryos？□Yes □ No

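### The live-birth comparison makes no use of age, a baseline value already on the case report form; pre-specified age adjustment is a small gain that needs no new data

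*Combined protocol and SAP*

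**What the plan says.** All references are to the combined protocol and SAP.

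- **11.2 Statistical methods** is the whole analysis plan. For categorical outcomes, including live birth, it says "Count data was analyzed using chi-square test". It names no covariate, regression model, stratified test or confidence interval for the treatment comparison.
- **5.2 Randomization** describes one computer-generated list of 1500 numbers split 1:1. No stratification factor is mentioned.
- **Section 6** enrols women aged 20 to 40. The Primary Screening Test Form has fields for date of birth and age. The eligibility item on "age at the time of informed consent" is only a Yes/No tick, so the usable value comes from the screening form.
- **4.2, 4.3 and 5.2** place screening on menstrual days 1 to 3 and allocation later, on the transformation day. Age is therefore a true baseline variable.
- **5.4** sets embryo limits by age and transfer history under Ministry of Health standards: "For subjects <35 years old with first embryo transfer, 2 embryos were allowed to transfer at most". Other women may receive 2 to 3. The case report form records the number transferred on the transfer-day form, after allocation.
- **11.1** sizes the trial with "Significance level α: 0.01", "Live birth rate in group A: 0.40" and "Live birth rates in group B: 0.30".

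**The concern.** When a baseline variable predicts a binary outcome, an analysis that uses it estimates the treatment difference somewhat more precisely than one that does not. It also accounts for any difference between the arms in that variable. Here the design does not balance age and the analysis does not use it, although the value is collected anyway. At stake are a little power and some robustness to an uneven age split. There is also a practical point. Section 5.2 makes allocation known to investigator and patient. If the arms turn out to differ in age, an adjusted result may be asked for after the data are seen, and 11.2 has no rule for producing one.

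**Working it through.** **Inputs from 11.1.** Rates 0.40 and 0.30, α 0.01 (sidedness not stated), power 0.90, ratio 1:1, 10% dropout.

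**Inputs assumed.** The strength of the age effect, an age SD of 4 years, a mean age of 31.5 in the linear simulation, and the share of women aged 35 or over. The documents give none of these.

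**Step 1: reproduce the plan's figure.** Two-sided, pooled variance, no continuity correction:

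n = [z(0.995)·√(2·0.35·0.65) + z(0.90)·√(0.40·0.60 + 0.30·0.70)]² / 0.10²
= (2.5758·0.6745 + 1.2816·0.6708)² / 0.01
= (1.7375 + 0.8597)² / 0.01 = 674.5, rounded up to 675.

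A one-sided calculation gives 590 and does not match. Dropout: 675/0.90 = 750. Both stated figures reproduce exactly, on the same unadjusted basis as the chi-square test.

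**Step 2: power by share of variance explained.** If age explains a share R² of the variance in live birth, the effective size is 675/(1 − R²), and power = Φ{[0.10·√n_eff − 1.7375]/0.6708}.

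| Assumed R² | Power at 675 per group | n per group for 90% | Reduction in SE |
|---|---|---|---|
| 0 | 90.0% | 675 | 0 |
| 1% | 90.4% | 669 | 0.5% |
| 2% | 90.7% | 662 | 1.0% |
| 5% | 91.7% | 642 | 2.5% |
| 10% | 93.2% | 608 | 5.1% |

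To judge which rows are plausible, R² ≈ (slope × SD)²/(0.35·0.65). With SD 4, a fall of 1, 2 or 3 points in live birth per year of age gives 0.04²/0.2275 = 0.7%, 0.08²/0.2275 = 2.8% and 0.12²/0.2275 = 6.3%. An R² of 10% needs √(0.10·0.2275)/4 = 3.8 points per year, or about 75 points across ages 20 to 40. The last row is therefore an extreme case.

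**Step 3: simulation at 675 per group, two-sided 0.01.**

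| Age effect assumed | Unadjusted power | Age-adjusted power | Gain (points) |
|---|---|---|---|
| Logistic, none | 89.9% | 89.9% | 0.0 |
| Logistic, odds ratio 0.78 per 5 years | 89.8% | 90.1% | 0.3 |
| Logistic, 0.61 | 90.4% | 91.5% | 1.1 |
| Logistic, 0.47 | 90.3% | 92.0% | 1.7 |
| Linear, none | 90.2% | 90.4% | 0.1 |
| Linear, 1 point per year | 90.2% | 90.8% | 0.6 |
| Linear, 2 points per year | 89.8% | 91.3% | 1.5 |
| Linear, 3 points per year | 90.1% | 92.2% | 2.2 |

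The logistic rows use 6000 replicates, so each power figure has a Monte Carlo SE of √(0.9·0.1/6000) = 0.4 points. The linear rows use 4000 replicates (0.5 points) and a robust SE for the adjusted risk difference. Gains are taken from unrounded values.

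**Step 4: chance imbalance.** With a share q aged 35 or over, the 95% limit on the between-arm difference in that share is 1.96·√(2q(1 − q)/675).

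- q = 0.20: 4.3 points. With a 5-point live-birth gap between age strata, the shift in the unadjusted difference is 4.27 × 0.05 = 0.2 points.
- q = 0.40: 5.2 points. With a 20-point gap, the shift is 5.23 × 0.20 = 1.05 points.

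The SE of the difference is √[(0.24 + 0.21)/675] = 2.6 points, so the larger shift is about 0.4 SE, against a planned effect of 10 points.

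**The case against.** The strongest objection is that this is a choice between two valid methods. Under randomisation the unadjusted chi-square keeps its type I error, its error rate already allows for chance imbalance, and it agrees with the basis of "675 cycles were required to reach 90% statistical power for each group". All of that stands. A reader might infer that the primary analysis is biased or the trial undersized; step 1 shows otherwise.

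The gain is also small, and several simulated gains are close to Monte Carlo error. The largest logistic gain needs an odds ratio of 0.47 per 5 years. With 35% live birth at the mean age, that means about 57% six years younger and 18% six years older. This stands too, and it sets the size of the point.

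A reader might take the embryo limits in 5.4 as the protocol's own statement that age is prognostic. It is not. The section attributes the limits to Ministry of Health standards, and allowing more embryos to older women could even flatten an age gradient. Age as a predictor remains an assumption.

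Nor does 11.2 leave the primary covariates open: naming one unadjusted test already fixes that analysis. Only an adjusted analysis requested later would lack a rule. Adjustment would also not remove chance imbalance in general. It accounts for imbalance in age, in the form modelled.

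Finally, regression in all randomised women needs a rule for unknown birth outcomes. That is true, but the chi-square in all randomised women needs the same rule, so it is not a cost of adjusting.

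**Conclusion.** The point holds as a minor improvement. The planned test is valid and consistent with the sample size, but it leaves unused a baseline value that is already collected. Over the age effects simulated, adjustment adds about 0 to 2 points to 90% power at 675 per group, with essentially no loss when age has no effect. The possible chance shift that it would account for is about 0.2 to 1.05 points. These sizes rest on assumed age slopes, an assumed age SD of 4 years and an assumed 20% to 40% of women aged 35 or over. Nothing here requires a change to the 675 or 750 per group.

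**What to change.** In 11.2, name the primary analysis: logistic regression of live birth on arm and age (continuous, from the screening form) in all randomised women. Report it as a standardised risk difference with a 95% confidence interval, by the delta method or bootstrap as stated in advance. This keeps the result on the 40% versus 30% scale used in 11.1; a conditional odds ratio alone would answer a different question. If the test is to be made at the 0.01 level of 11.1, give the matching 99% interval as well. Keep the chi-square as the supporting unadjusted result.

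Do not add number of embryos. The transfer-day form records it after allocation, and no form records a planned number before allocation.

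The cost is a few sentences in 11.2. It needs no new data, no further patients and no change to the forms.

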# 12 Adverse event reports

## 12.1 Risks and discomfort

This study doesn’t have any additional risks and discomfort. The following table lists the possible risks and discomfort during the study.

| **Events** | **Risks and discomfort** |
| --- | --- |
| Thawing embryo | Embryo recovery failed and 95% of recovery success rate |
| Embryo transfer | Infection |
| Transvaginal ultrasound | Discomfort in abdominal or pelvis |
| Administration of sustained release vaginal progesterone gel | Vaginal itching and other symptoms |
| Intramuscular progesterone | Injection pain and injection site may occur abscess and panniculitis and allergic reactions |
| Ectopic pregnancy | Ectopic pregnancy may be required. If the treatment is delayed, parts of pregnancy may rupture leading to intraperitoneal blooding and even shock or death in severe conditions. |
| Multiple pregnancies | Fetal reduction may be performed, increasing the risks of pregnancy complications, fetal malformations and preterm birth. |
| Infertility treatment | Anxiety and bad mood at varying degrees |

Patients will be randomly assigned to a group and the curative effect in this group may be worse than in the other group. But, investigator will try to avoid the occurrence of such risks and discomfort. If that happens, patients will be treated promptly and charged routinely. This study does not provide any free treatment and financial compensation.

## 12.2 Definition of adverse event

Adverse event refers to the subjects participating in the study suffered any unexpected or adverse medical events, whether or not related to the study intervention. Adverse events may be any of the following:

- Signs or symptoms, including side effects of drugs;
- Abnormal laboratory parameters;
- Changes in vital signs, physical examination or test results;
- Frequency or extent (deterioration) of previous symptoms or diseases before recruitment increasing during the study.

Adverse events in this study do not include:

- Previous symptoms or diseases before recruitment without worsen during the study;
- Normal reactions related to pregnancy

Serious adverse events include any of the following occurred during the study:

- Death
- Life-threatening (there is a risk of immediate death)
- Severe or permanent disability
- Hospitalization required or prolonged
- Neonatal death at 6 weeks postpartum
- Newborns with severe congenital anomaly or birth defect
- Investigator regarding the events as serious events

